## Abstract

**Background:**

A crucial issue for the sustainability of societies is how to maintain health and functioning in older people. With increasing age, losses in vision, hearing, balance, mobility and cognitive capacity render older people particularly exposed to environmental barriers. A central building block of human functioning is walking. Walking difficulties may start to develop in midlife and become increasingly prevalent with age. Life-space mobility reflects actual mobility performance by taking into account the balance between older adults internal physiologic capacity and the external challenges they encounter in daily life. The aim of the Life-Space Mobility in Old Age (LISPE) project is to examine how home and neighborhood characteristics influence people’s health, functioning, disability, quality of life and life-space mobility in the context of aging. In addition, examine whether a person’s health and function influence life-space mobility.

**Design:**

This paper describes the study protocol of the LISPE project, which is a 2-year prospective cohort study of community-dwelling older people aged 75 to 90 (n = 848). The data consists of a baseline survey including face-to-face interviews, objective observation of the home environment and a physical performance test in the participant’s home. All the baseline participants will be interviewed over the phone one and two years after baseline to collect data on life-space mobility, disability and participation restriction. Additional home interviews and environmental evaluations will be conducted for those who relocate during the study period. Data on mortality and health service use will be collected from national registers. In a substudy on walking activity and life space, 358 participants kept a 7-day diary and, in addition, 176 participants also wore an accelerometer.

**Discussion:**

Our study, which includes extensive data collection with a large sample, provides a unique opportunity to study topics of importance for aging societies. A novel approach is employed which enables us to study the interactions of environmental features and individual characteristics underlying the life-space of older people. Potentially, the results of this study will contribute to improvements in strategies to postpone or prevent progression to disability and loss of independence.

## Background

Walking, driving and using public transport are the leading forms of mobility among older adults in their local neighborhood. Walking is an integral part of mobility and may be considered a prerequisite for the unassisted use of other modes of transportation. Consequently, the different modes of mobility may share similar risk factors. Mobility is optimal when you are able to go where you want to go, when you want to go, and how you want to go, safely and reliably
[1].

The proportion of people over 80 years is growing rapidly. The majority of older people lives in private households and, along with increasing age and declining health, tend to spend more and more of their time inside the home or in its immediate surroundings. Eventually, mobility limitations may render them homebound which, in turn, may lead to marginalization from social activities, loneliness and poor quality of life
[2]. A better understanding of the factors that hinder or support the independent community mobility of older people is required to optimize opportunities for active aging and to reduce health disparities.

The disablement model by Nagi
[3], later expanded by Verbrugge and Jette
[4], outlines the pathway between pathology and disability. Pathology refers not only to physiological abnormalities, such as chronic diseases or injury, but also to physiological changes with advancing age that affect specific body systems and may result in impairments such as strength, balance or sensory impairments. Impairments may lead to functional limitations such as decreased gait speed, which in turn may cause disability. Disability refers to a situation where individual capabilities are not sufficient to meet the requirements of the living environment. The ecological model of ageing, also known as the “Competence-Press model”
[5], describes the person-environment relationship in more detail. Environmental factors influence mobility through interaction with the individual’s capabilities, termed person-environment fit (P-E fit). If an individual’s competence and the demands of the environment are in balance, then that individual is able to adapt and function optimally. The ecological model of aging has a strong psychological emphasis, while the disablement process model emphasizes physiological changes. Combining the salient aspects of these two models into an analytical approach may provide a good foundation to better understand age-related changes in mobility.

In the long term, most of the chronic conditions that accompany aging will have a detrimental influence on mobility through various mechanisms involved in the decline in functioning of the musculoskeletal, neurological or cardio-respiratory systems. The impairments most commonly studied in relation to walking difficulties are those that directly influence walking, namely muscle strength and balance. Impairments in sensory functions, such as vision and hearing, also affect mobility
[6]. Hearing loss may hinder the ability to divide attention between traffic, having a conversation, maintaining postural balance and walking, thus potentially increasing risk for falls and other accidents
[7]. According to one of our previous studies
[8], people with co-existing vision and hearing impairments had over four-fold risk, and people with co-existing impairments in vision, hearing and balance almost 30-fold risk, for falls, compared to people with no vision impairment. Falling and fall-related injuries are common among older people, often leading to a sudden and catastrophic disability. Approximately 20% to 40% of community-dwelling individuals older than 65 years fall every year and about half of those who fall do so repeatedly
[9]. Falls may lead to progressive mobility decline, even in the absence of consequent injury. In our previous study, older women with indoor falls were over three times more likely to report new difficulties in walking 2 km by the end of the 3-year follow-up compared to those with no falls
[10].

Environmental conditions affect outdoor mobility, especially in older adults
[11], either by facilitating or restricting participation in out-of-home activities. Environmental barriers for outdoor mobility subjectively reported by older adults include, for example, poor transportation, discontinuous or uneven side-walks, curbs, noise, heavy traffic, inadequate lighting, lack of resting places, sloping terrain, long distances to services and weather conditions
[12,13]. Poor street condition, heavy traffic and excessive noise correlate with onset of mobility limitation while pedestrian-oriented designs and access to recreational facilities are positively associated with physical activity and self-rated health in older adults. Similar evidence exists for the association between barriers in the home and difficulties carrying out important daily activities
[14]. However, most of the existing studies are cross-sectional. This makes it impossible to know which comes first, the environmental barrier or the mobility problem, and so draw conclusions on causality (for review, see
[15]).

Life-space mobility refers to the size of the spatial area (bedroom, home, outside home, neighborhood, town, distant locations) a person purposely moves through in daily life and to the frequency of travel within a specific time and need of assistance for that travel
[16]. The first reports on life-space appeared in the aging literature during the 1980s and early 1990s
[17,18], but most studies concerned nursing home residents. Life-space mobility reflects the balance between the persons’ internal physiologic capacity and the environmental challenges older adults encounter in daily life. Life-space can be used to evaluate transitions in individuals’ abilities to live independently
[16]. Only few studies have addressed life-space mobility in community-living older people
[19]. Shrinking life-space probably coincides with giving up valued activities that, maintain the social role of the person, such as visiting friends, participating in out-of-home hobbies, recreation or work, and in general with giving up accessing community amenities, a situation referred to as participation restriction
[20]. However, not all older persons with functional limitations necessarily restrict their life-space, if they can find ways to compensate for their difficulties, e.g. by using mobility devices
[21]. Consequently, measuring life-space mobility also needs to incorporate compensatory strategies.

## Project aims

### Study aim

The aim of the Life-Space Mobility in Old Age (LISPE) project is to examine how home and neighborhood characteristics influence the residents’ health, functioning, disability, quality of life and life-space mobility in the context of aging.

Specific research questions are:

1. What are the environmental (e.g. distance to services, green spaces, benches by walk ways, heavy traffic, level of urbanization) and individual (e.g. fear of moving outdoors, fear of falling and injury, sensory impairments, walking limitation, personal goals) determinants of life-space mobility, disability and participation restriction?

2. Does life-space mobility correlate with indicators of individual wellbeing (quality of life, depressive symptoms and perceived health)?

3. Do changes (increase, decrease) in life-space mobility lead to parallel changes in indicators of individual wellbeing?

4. What are the environmental and individual predictors of changes in life-space mobility and disability (onset, recovery) and participation restriction?

5. How do facilitating/supporting or encumbering environmental features (perceived and objective) differ according to the extent of life-space mobility or differences in functioning?

6. Do individual and environmental features interact in explaining life-space mobility?

7. What are the individual and environmental factors and their interactions underlying the association of life-space mobility and quality of life in older people?

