### Measures

Age and gender were drawn from the population register as part of the sampling procedure. All the other measures and their time of assessment are listed in Table
1.

**Table 1 T1:** Measures included in the study and the number of items included in each follow-up

**Instrument**	**Domains**	**Assessment**			
		**BL**	**FU1**	**FU2**	**Ref.**

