**Participation**					
Leisure time activities		5 items	-	-	[32]
Impact on Autonomy & Participation (IPA)	Autonomy outdoors	5 items	-	-	[33,34]
Disability in self-care & instrumental activities	ADL	5 items	-	5 items	[35]
	IADL	9 items	-	-	
	Additional items	2 items	-	-	

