#### Impact on participation and autonomy

The Impact on Participation and Autonomy questionnaire (IPA)
[33] is a validated questionnaire designed to assess perceived autonomy and participation in various clinical as well as older populations. It consists of 5 domains: social relations, autonomy in self-care, autonomy outdoors, family role, and work and educational opportunities. For this study, only the domain “autonomy outdoors” was used. Participants were asked to rate perceived chances in 1) visiting relatives and friends, 2) making trips and traveling, 3) spending leisure time, 4) meeting other people, and 5) living life the way they want. The response categories ranged from 0 (very good) to 4 (very poor). A sum score was calculated, with a higher score indicating more restrictions in participation. For participants with one missing item, the total score was calculated (n = 2). An official Finnish translation was used
[34].

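### Table 1 schedules the participation-restriction measures at baseline only, which contradicts the participation-restriction part of research question 4 and the Abstract's follow-up sentence

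*Protocol article*

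**What the plan says.** Three places in the protocol article bear on this.

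- **Study aim, research question 4:** "What are the environmental and individual predictors of changes in life-space mobility and disability (onset, recovery) and participation restriction". Question 1 separately asks for the determinants of participation restriction, without reference to change.
- **Abstract, Design:** all baseline participants "will be interviewed over the phone one and two years after baseline to collect data on life-space mobility, disability and participation restriction".
- **Measures and Table 1:** the text introduces the table with "All the other measures and their time of assessment are listed in Table" 1, age and gender being the only exceptions. In the Participation block, the columns being baseline, one year and two years, the relevant rows read "Impact on Autonomy & Participation (IPA) Autonomy outdoors 5 items - - [33,34" and "Leisure time activities 5 items - - [32".

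The section on the IPA explains what that scale is for: "A sum score was calculated, with a higher score indicating more restrictions in participation". Only its autonomy-outdoors domain is used.

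The section on relocation and other major life events adds a semi-structured interview at both follow-ups. Hobbies taken up or ended are among its examples.

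**The concern.** A question about predictors of change needs the outcome at two time points or more. Participation restriction is named as such an outcome, and the Abstract tells the reader that it is collected twice after baseline. The assessment schedule shows no follow-up measurement of it. If the schedule is right, a stated longitudinal aim cannot be met with the IPA or the leisure-activity items, and only a cross-sectional association at baseline could be reported. No analysis plan could repair this, because the data would not exist, and a follow-up wave that has passed cannot be recovered. If the schedule is wrong, the design may be sound, but the table misinforms anyone who relies on it.

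**Working it through.** The plan states no figure on this point, and no power or sample-size formula applies. The check is a comparison of the stated aims with the schedule.

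**Step 1: which measure represents participation restriction?** The Background describes the concept as giving up valued activities and access to community amenities. Of the instruments described, only the IPA autonomy-outdoors sum is scored in those terms. Leisure time activities is the other participation measure. Basic and instrumental ADL stand under the same table heading, but the article describes them as disability in self-care and instrumental activities.

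**Step 2: when is each outcome of question 4 measured?** Item counts from Table 1:

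| Measure | Baseline | 1 year | 2 years | Time points |
|---|---|---|---|---|
| IPA, autonomy outdoors | 5 | none | none | 1 of 3 |
| Leisure time activities | 5 | none | none | 1 of 3 |
| Life-space mobility (5 levels × 3 items) | 15 | 15 | 15 | 3 of 3 |
| Difficulty walking 2 km | 1 | 1 | 1 | 3 of 3 |
| Difficulty walking 500 m | 1 | 1 | 1 | 3 of 3 |
| Basic ADL | 5 | none | 5 | 2 of 3 |

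**Step 3: can change be formed?** Change needs at least 2 time points. The IPA and leisure rows have 1, so the number of change scores available on either scale is 0 of 848. Life-space mobility and the two walking items have 3, and basic ADL has 2, so the other two outcomes named in question 4 can be analysed for change.

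**Step 4: could this be a fault of text extraction?** It does not look like one. The IPA and leisure rows are intact, and the ADL row in the same block does show a two-year entry.

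**Step 5: does anything else at follow-up fill the gap?** The nearest item is the life-event probe on hobbies. It asks about events since the previous assessment, so it touches change directly. However, it is semi-structured, gives no restriction score, and is presented as something that may influence life-space mobility, not as an outcome.

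**The case against.** The best case on the other side has five parts.

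- **Table 1 may be what is wrong.** If the IPA items are in the follow-up questionnaires and the table omits them, only the table needs correcting. This stands. A reader might infer that the Abstract's statement is untrue, but the article supports only the weaker claim that the Abstract and Table 1 contradict each other.
- **The hobby probe is follow-up information on participation.** This stands in part. It is why the conclusion is limited to the IPA and leisure scales. It does not supply a measured change in participation restriction.
- **The word changes in question 4 might not govern participation restriction.** On that reading this part of question 4 would largely repeat question 1, and the Abstract's sentence would still conflict with Table 1.
- **Disability is not affected.** A reader might infer that it has the same defect, because instrumental ADL is taken at baseline only and basic ADL is skipped at one year. The documents do not support that. Question 4 asks for onset and recovery and does not promise three waves of every disability measure. The walking items (three waves) and basic ADL (baseline and two years) are enough for that purpose. The Abstract's promise of disability data at one and two years is met by the walking items. The authors also say that they limited interview length to spare participants.
- **Participation restriction is not a main outcome.** This stands. The main outcomes are life-space mobility and quality of life, and the overall aim does not name participation restriction. It is one of three outcomes in one of seven questions.

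**Conclusion.** The contradiction is real and confined. On the schedule in Table 1, change in participation restriction cannot be computed on the IPA or on the leisure-activity items, so the participation-restriction part of question 4 cannot be answered with them. The Abstract's follow-up sentence is contradicted on the same point. The rest of question 4 is unaffected, and the baseline IPA still serves the cross-sectional question 1.

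A reader might go further and call question 4 as a whole unanswerable. That does not follow, since life-space mobility and disability are both measured repeatedly.

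The conclusion rests on taking Table 1 as the complete schedule, as the Measures section says it is. It should be fixed, because it changes what the study can claim about a named outcome. It does not bear on the validity of the main results.

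**What to change.** Establish what the follow-up interviews actually contain, then bring the three places into line.

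1. **If the IPA items are already in the follow-up questionnaires:** correct Table 1. This costs nothing beyond the edit.
2. **If they are not, and the waves are still open:** add the 5 autonomy-outdoors items to the one-year and two-year telephone interviews, at minimum the two-year one, and correct Table 1. The cost is 5 items per call, 10 per participant over both calls, or a few minutes of respondent time. The article writes of both follow-ups in the future tense but gives no dates for them, so whether the one-year calls can still be changed has to be checked.
3. **If the items will not be collected:** remove participation restriction from question 4 and from the Abstract's follow-up sentence, and confine it to question 1. The cost is a narrower stated aim.

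The disability measures need no change on this account.

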### Substudy aim

The aim of the substudy is to investigate the relationship between habitual walking activity and life-space mobility among community-dwelling older people with an emphasis on environmental barriers and facilitators to habitual walking activity.

## Methods

### Study design

The study is a 2-year prospective cohort study of community-dwelling older people aged 75 to 90 living in the municipalities of Muurame and Jyväskylä, Finland. Over the 2-year period, four personal contacts will be made with the participants, as shown in Figure
1. The initial contact over the phone was followed by a baseline interview at the home of the participant within 1 to 2 weeks. The baseline home visit will be followed up by phone interviews one and two years later. Subsequently, participants who have relocated since the previous assessment will be visited by a research assistant to gain additional information regarding their relocation and new living environment. The study also provides an opportunity to collect data on the use of health services and on the mortality of the participants from national registers. The substudy on walking activity and life-space mobility was conducted immediately following the baseline assessment.

**Figure 1 F1:**
[figure not shown]
**Conduct of the study.** The diary as well as the home visit at follow-up 1 (FU1) and 2 (FU2) only concern subgroups of participants and are colored gray. Recr. refers to recruitment and BL to baseline assessment.

Muurame and Jyväskylä are neighboring municipalities located in central Finland with total population of 141 500. At the time of drawing the sample, the total population of men and women within that age range was 8 914, of whom 7% lived in sparsely populated areas. For each age group of 75–79, 80–84, and 85–89 years, a random sample of 500 was drawn from the population register on December 12^th^, 2011. The sample was supplemented on March 15^th^, 2012 with an additional 350 persons for each age group to secure a sufficient number of participants. The resulting sample was thus 2 550.

#### Sample size calculations

We calculated that our sample size needed to be at least N = 800 to have sufficient power to also run analyses for subgroups based on age, gender and type of neighborhood. For continuous variables (e.g. life-space mobility variables) a sample size of 800 yields a power of > 99% to show a contribution to the explained variance of 5% in a linear regression model with 10 predictors (including interactions, but not constant) if the probability level (alpha) is set at 0.05. In addition, a sample size of 800 yields even weak correlation coefficients statistically significant. Based on the population characteristics of the recruitment area, 7% of the included population was expected to be living in a sparsely populated area. With a total sample size of at least 800 this would yield a subgroup of about N > 56 persons. In the univariate analyses, correlation coefficients of r > 0.3 would be statistically significant with a two-tailed significance level of 0.05 and a sample size of 56.

### Recruitment process and data collection

#### Contacting participants

A letter containing information about the study including an announcement to expect a phone call the following week was sent to the potential participants. Phone numbers were collected from a nationwide database for all persons in the sample. The research assistant ([name]) called potential participants by phone at the time indicated. When a person could not be contacted, at least 5 repeat phone calls were made on different days and times. When no phone number was available for a person, an information letter was sent including a request to call our research assistant if interested in participating in the study.

### The initial phone interview

During the first phone call potential participants were asked about their willingness to participate in the study and to respond to a short questionnaire with the aim of determining, whether the person was eligible for participation in the study. The inclusion criteria were living independently, able to communicate, residing in the recruitment area and willing to participate. If a person was found eligible, the time for the home visit was set. A letter confirming the time of the home visit was mailed to the participant’s home accompanied by an informed consent form. Persons not interested in participating in the study were asked whether they wished to respond to the same brief phone interview questionnaire as the participants. These data will be used for a non-respondent analysis. The main reason for non-participation (poor health or illness, lack of time, or unwillingness) was recorded if clearly indicated by the person.

